# A prospective randomized double-blind trial of the efficacy of a bilateral lumbar erector spinae block on the 24h morphine consumption after posterior lumbar inter-body fusion surgery

**DOI:** 10.1186/s13063-019-3541-y

**Published:** 2019-07-17

**Keywords:** Erector spinae block, Lumbar inter-body fusion, Regional anesthesia, Postoperative pain

## Abstract

**Background:**

Spine surgery is associated with considerable postoperative pain and can be challenging to treat. A loco-regional technique suitable for spine surgery should cover the dorsal root of the spinal nerves at the levels where surgery is performed. The erector spinae block is a loco-regional technique with promising results and was recently described at the thoracic level. There are no randomized trials of this technique on a lumbar level. This study tests the hypothesis that the 24-h postoperative morphine consumption is significantly lower in patients undergoing posterior lumbar inter-body fusion surgery with a lumbar erector spinae (LUMBES) block when compared with a sham block.

**Methods:**

This prospective randomized double-blind multicenter study will randomly allocate 80 adult patients undergoing elective posterior lumbar inter-body fusion surgery during general anesthesia to one of two groups as follows: (1) bilateral erector spinae block (20 mL 0.25% levobupivacaine) or (2) bilateral sham block (20 mL NaCl 0.9%). Our primary endpoint is 24-h postoperative morphine consumption. Secondary endpoints include 72-h morphine consumption, intraoperative sufentanil dosage, postoperative pain scores at regular time intervals both at rest and during movement, time to first postoperative mobilization, and the Quality of Recovery 40 survey score.

**Discussion:**

The LUMBES trial is a pragmatic clinical study that will provide evidence of whether a bilateral lumbar erector spinae block is effective in reducing 24-h postoperative morphine consumption in patients undergoing lumbar inter-body fusion surgery. If this hypothesis is confirmed, this finding could contribute to more widespread implementation of this technique.

**Trial registration:**

Local ethics committee B300201837508, ClinicalTrials.gov identifier: NCT03825198. Registered on 31 Jan 2019.

**Electronic supplementary material:**

The online version of this article (10.1186/s13063-019-3541-y) contains supplementary material, which is available to authorized users.

## Background

### Background information

Patients undergoing spine surgery often fear postoperative pain, which can be a source of considerable preoperative distress. In many of these patients, so-called chronic pain, requiring high doses of narcotics and other analgesics, has already been diagnosed. In spine surgery, postoperative pain can often be severe and difficult to treat, certainly if a one-dimensional approach is used to achieve pain control [1, 2]. Many caregivers are reluctant to prescribe liberal doses of opioids to achieve adequate analgesia as this may be associated with side effects such as respiratory depression, sedation, and nausea. Many techniques have been combined in order to decrease opioid consumption after spinal surgery (e.g., epidural catheters, spinal and epidural morphine, or local infiltration) [3]. The introduction of ultrasound has allowed the performance of plane blocks and other techniques such as root blocks and facet infiltrations without the use of unreliable “pop-techniques” or x-ray.

**Fig. 1 Fig1:**
[figure not shown]
Recommended content for the schedule of enrollment, interventions, and assessments*

A loco-regional technique suitable for back surgery should cover the innervation of the relevant vertebrae and paravertebral muscles and include the dorsal roots of the spinal nerves at this level [4]. Dorsal ramus blocks have been shown to be feasible in the treatment of chronic back pain [5].

Recently, a series of case reports has been described in which bilateral block of the lumbar dorsal ramus nerve resulted in a positive effect on pain scores and morphine consumption after spine surgery [6]. However, to the best of our knowledge, no randomized controlled trials have yet been performed to study the effect on pain scores and opioid consumption. Furthermore, there are promising results for postoperative analgesia with a new plane block, the erector spinae block (ESB), which has recently been described as a safe and simple technique for neuropathic and acute postoperative pain at the thoracic level [7, 8].

### Rationale

Theoretically, an infiltration between the erector spinae muscle and the transverse process provides anesthesia of the dorsal ramus at the same vertebral level. Since the local anesthetic is injected into a plane, the solution can spread both caudally and cranially via the thoracolumbar fascia, resulting in anesthesia of the dorsal ramus of the spinal nerves above and below the injected level. The ESB has been described at the thoracic level with promising results. We performed a small feasibility trial in which we found that the ESB could easily be performed without major inconvenience for the patients (ClinicalTrials.gov identifier: NCT0321453). In this proposed trial, we aim to determine the effect of a lumbar ESB on pain after back surgery, expressed as morphine consumption during the first 24 h postoperatively.

### Objectives and purpose

In this prospective, randomized, double-blind placebo-controlled clinical trial, we will investigate the effect of bilateral ESB (20 mL of levobupivacaine 0.25%) on 24-h postoperative morphine consumption when compared with a sham block (20 mL of NaCl 0.9%) following posterior lumbar inter-body fusion surgery. Secondary objectives include the effect of the ESB on the numeric rating scale (NRS) pain scores in rest at fixed time points: at the time of inclusion, in the post-anesthesia care unit (PACU) (T0 = arrival in PACU, T + 15 min, T + 30 min), and on the ward (twice daily: morning and evening until postoperative day 3). Other secondary objectives are the effect of an ESB on the NRS pain scores during defined movement (mobilization to chair) at 24 h, 48 h, and 72 h; time to first mobilization to chair (hours); time to first walk of 20 m (hours); the required sufentanil dose during surgery (micrograms), total morphine consumption during the first 72 h postoperatively (milligrams), and the Quality of Recovery 40 survey (QoR-40) score at days 1 and 3.

## Methods/Design

### Study design and registration

This is an investigator-initiated prospective randomized double-blind multicenter trial. The study is being performed in accordance with the Declaration of Helsinki (Fortaleza, Brazil; October 2013) and Good Clinical Practice (GCP) guidelines. The study has been approved by the ethics committee at Antwerp University Hospital, Wilrijk, Belgium, and AZ Klina Hospital, Brasschaat, Belgium (reference: B300201837508). The trial has been prospectively registered at https://www.clinicaltrials.gov (reference: NCT03825198) and will be monitored by the clinical trial center of Antwerp University Hospital. Figure 1 displays the schedule of enrollment, interventions and assessments.

### Participation

Patients scheduled for elective 1 or 2 level posterior lumbar inter-body fusion surgery in AZ Klina Hospital and Antwerp University Hospital will be asked for informed consent by a member of the anesthesiology department. Recruitment will occur during the preoperative consultation; it opened on July 9 , 2019, and will close when the required number of patients has been reached.

Inclusion criteria are as follows: (1) American Society of Anesthesiologists (ASA) physical status of 1–3, (2) age of 18–75 years, and (3) normal liver and renal function.

Exclusion criteria are as follows: (1) body mass index (BMI) of less than 20 or BMI of more than 35; (2) allergy to one or more medications used in the study, including epinephrine, levobupivacaine, dexamethasone, propofol, sufentanil, rocuronium, ketorolac, morphine, ketamine, dehydrobenzperidol, ondansetron, and alizapride; (3) chronic strong opioid use (>3 administrations per week); (4) contraindications to a regional anesthetic technique; and (5) patient refusal or no informed consent or both.

### Randomization

Patients will be assigned consecutive numbers upon inclusion in the study. These numbers are randomly allocated (1:1) to the ESB or the sham group by using a web-based randomization system, QMinim. QMinim uses stratified randomization, and stratification will be carried out according to site, gender, and levels of surgery. In QMinim, a minimization procedure is used to randomly assign the patients to ensure a similar distribution of the stratifying arms. Online randomization will be carried out by an independent anesthetist who will also prepare the medication.

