### Patient characteristics and baseline comparisons

Demographic and other baseline characteristics will be summarized by treatment group. For categorical variables, frequencies and percentages will be reported. Where values are missing, percentages will be calculated for the available cases, and the denominator will be mentioned. Continuous variables will be summarized as mean with standard deviation or median with interquartile range as appropriate.

Comparisons of demographic and baseline characteristics between the treatment groups will be conducted to assess the effectiveness of randomization. For categorical variables, the chi-squared test or Fisher exact test (when numbers are low) will be used. For continuous variables, a *t* test or Mann–Whitney *U* test will be used as appropriate. The following baseline information prior to randomization will be collected: age, sex, BMI, ASA physical status, indication for surgery, preoperative pain (NRS score), and use of analgesics.

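### Preoperative opioid use is neither a minimisation factor nor in the unadjusted primary test, although analgesic use is recorded before randomisation: a loss of precision, not a bias

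*Protocol article*

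**What the plan says.** - **Eligibility (Participation).** The only opioid-related exclusion is "chronic strong opioid use (>3 administrations per week". The inclusion criteria concern ASA status, "2) age of 18–75 years, and (3) normal liver and renal function"; none restricts opioids. Weak opioids at any frequency, and strong opioids up to three times a week, are therefore allowed.
- **Allocation (Randomization).** Allocation is 1:1 by minimisation in QMinim, and "stratification will be carried out according to site, gender, and levels of surgery". Opioid use is not on the list.
- **Baseline data (Patient characteristics and baseline comparisons).** The items collected before randomisation include "indication for surgery, preoperative pain (NRS score), and use of analgesics".
- **Analysis (Analysis of the endpoints).** The primary endpoint, 24-h morphine from the PCIA pump, is compared by an independent-samples t test in the intention-to-treat population if the data are normal. A linear regression allowing for possible confounders serves as a sensitivity analysis, and those confounders are not named.
- **Background information.** Many spine-surgery patients are said to have chronic pain already, needing high doses of narcotics and other analgesics. No prevalence is given.

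**The concern.** Prior opioid use is a plausible predictor of postoperative morphine consumption, which is the primary endpoint itself. The exclusion of frequent strong-opioid users suggests that the investigators see the link, though the article gives no reason for that exclusion. What remains after the exclusion is a mixed population, and two places where the mix could be handled do not handle it: the minimisation and the primary test.

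Two things are at stake. First, variation between users and non-users stays in the error term, so power is lower than the collected data would allow. Second, if one arm happens to receive more users, the primary estimate carries that imbalance. The correction would then come only from a secondary model, and the article does not say that this model will contain opioid use.

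**Working it through.** **1. The plan's own figure.** Inputs from Sample size: mean 51 mg, SD 19 mg, 25% reduction, alpha 5%, power 80%.

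- Target difference: 0.25 × 51 = 12.75 mg.
- n per group = 2 × (1.960 + 0.842)² × 19² / 12.75² ≈ 34.9, so 35. This matches the article, read as a two-sided test.
- With the noncentral t distribution, power is 79.0% at 35 per group and 84.2% at 40, and 36 per group are needed for 80%. The difference from 35 is trivial.
- Standard error of the mean difference at 40 per arm: 19 × √(2/40) = 4.25 mg.

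**2. Assumed inputs.** The article gives neither the share of users (p) nor their excess morphine need (m). I take p from 20% to 50% and m from 5 to 20 mg. The SD of 19 mg is read as the total spread between patients.

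**3. Gain from balancing and adjusting.** Share of variance explained: R² = p(1 − p)m² / 19². Residual SD = 19 × √(1 − R²). For p = 30% and m = 15 mg: R² = 0.21 × 225 / 361 = 0.131, and the residual SD is 17.71 mg. Power at 40 per arm (noncentral t, 12.75 mg difference):

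| Excess m | p = 20% | p = 30% | p = 50% |
|---|---|---|---|
| none (unadjusted) | 84.2% | 84.2% | 84.2% |
| 5 mg | 84.6% | 84.7% | 84.8% |
| 10 mg | 85.8% | 86.3% | 86.7% |
| 15 mg | 87.8% | 88.9% | 89.7% |
| 20 mg | 90.5% | 92.3% | 93.6% |

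If dropout leaves 35 per arm, power rises from 79.0% to between 80.8% (p = 20%, m = 10 mg) and 90.2% (p = 50%, m = 20 mg).

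**4. Chance imbalance without balancing.** This treats allocation as unrelated to opioid use, with 40 per arm and a hypergeometric distribution. For p = 20-50%, the arms differ in their share of users by at least 10 points with probability 40-50%, and by at least 20 points with probability 5-12%. A 20-point difference moves the estimate by 0.20 × 10 = 2 mg to 0.20 × 20 = 4 mg, or 16-31% of 12.75 mg.

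**5. Does balancing add much to adjusting?** At p = 30%, a 20-point imbalance gives a correlation between treatment and opioid use of 0.20 / (2 × √0.21) = 0.218. Adjusting without balancing then inflates the standard error by 1 / √(1 − 0.218²) = 1.025, about 2.5%. Nearly all the gain comes from the model.

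**The case against.** Nothing in the allocation is wrong. Three factors are a reasonable choice for 80 patients, and age, BMI or baseline pain could be proposed as a fourth with similar arguments. The group most likely to distort morphine use is already excluded. The article provides a covariate-adjusted regression, and naming its covariates is commonly left to an analysis plan that is not shown. Every magnitude here rests on assumed inputs.

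Most of this stands. It is why the point concerns precision and why a new minimisation factor is not required. What it does not answer is that the article fixes the primary test as unadjusted. Naming covariates later would improve only the sensitivity analysis.

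A reader might go further and infer that the trial is biased or its randomisation defective. The documents do not support that: "These numbers are randomly allocated (1:1) to the ESB or the sham group" describes a valid allocation, the expected imbalance is zero, and the type I error is preserved.

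A reader might also treat chance imbalance as error on top of the planned uncertainty. With 30% users needing 15-25 mg more, the 95% range of the shift is 1.96 × √(2 × 0.3 × 0.7 / 40) = 0.201 times the excess, or ±3.0 to ±5.0 mg. That is an extreme, not a typical value. If the SD of 19 mg is the total spread, it is already contained in the ±8.3 mg (1.96 × 4.25) that the unadjusted estimate carries. The upper input also requires one yes/no variable to explain 0.21 × 625 / 361 = 36% of the variance after the heaviest users are excluded, and nothing in the article supports that.

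**Conclusion.** The point holds as a limited, inexpensive gain in precision. The criteria leave a mix of opioid exposure, and neither the minimisation nor the primary test uses a baseline item that the trial already collects. No number in the protocol is wrong on this point, and the sample size need not change.

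The size depends on inputs that the article does not give. With 20-50% users and a 10-20 mg excess, power at 40 per arm goes from about 84% to about 86-94%. With a 5 mg excess the gain is under one point. These figures assume that 19 mg is the total SD, that all 80 patients contribute, and that the factor is both balanced and modelled. Adjustment alone gives slightly less.

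One further inference is involved: the article records use of analgesics and does not name opioids separately, so the yes/no variable must be derivable from that history.

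**What to change.** In Analysis of the endpoints, make the primary analysis of 24-h morphine a linear regression on treatment, preoperative opioid use (yes/no), site, gender and levels of surgery. Keep the unadjusted t test as the sensitivity analysis. The treatment effect remains a difference in mean milligrams.

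Define opioid use in writing, before unblinding, from the analgesic history taken at inclusion. Check that the record form distinguishes opioids from other analgesics.

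The cost is a short amendment and one derived variable, with no new visits or patients. The model uses a few degrees of freedom: 80 − 6 = 74 instead of 78.

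Optionally, add opioid use as a fourth QMinim factor for the remaining patients. Participation gives July 9, 2019 as the opening of recruitment, so this would change allocation in a running trial. Patients already randomised would have to be entered retrospectively, and balance on the other three factors would become slightly looser. Since adjustment recovers nearly all the benefit, the trial can do without this step.

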### Medication

The ESB study medication will be 20 mL of levobupivacaine 0.25% (Chirocaine, AbbVie, Lake Bluff, IL, USA). The sham group received 20 mL of NaCl 0.9% (B. Braun, Melsungen, Germany).

### Blinding

All investigators, staff, and patients will be blinded to the treatment groups. The study medication will be prepared by an anesthesiologist who is not involved in the study or in the care of the patient. Both solutions and syringes will appear identical. Unless medically indicated, unmasking will occur only after statistical analysis has been completed.

### Interventional treatment

All patients will receive a bilateral ESB. The blocks will be performed by experts in the field of ultrasound-guided regional anesthesia. The blocks will be performed preoperatively in a separate block room with ultrasound after obtaining intravenous (IV) access and application of standard ASA monitoring. The blocks will be placed as described by Chin et al. [6] and modified for the lumbar level. The patient will be placed in the lateral or sitting position. A curved array probe or a high-frequency linear probe, depending on the BMI of the patient, will be placed in longitudinal alignment, 2–3 cm lateral to the vertebral column. The transverse processes of the vertebrae at the level of surgery, the erector spinae muscle, and the psoas muscle will be identified. In case of two-level surgery, the transverse process of the upper level will be considered the target. A 5- or 8-cm 22-G ultrasound needle will be inserted with an in-plane technique in a cephalad-to-caudal direction until bone contact with the top of the transverse process is reached. After slight retraction of the needle, 20 mL of the study medication will be injected behind the erector spinae muscle. The same procedure will be repeated on the contralateral side.

Then general anesthesia—propofol 2–3 mg/kg, sufentanil 15 μg, and rocuronium 0.5 mg/kg—will be induced in a standardized way. After tracheal intubation, anesthesia will be maintained with sevoflurane and intraoperative analgesia provided with sufentanil. The dosages of these agents will be determined at the discretion of the attending anesthesiologist. At the end of surgery, patients will receive acetaminophen 1 g IV, ketorolac 0.5 mg/kg IV (maximum of 30 mg), and a morphine loading dose (0.1 mg/kg) IV to manage postoperative pain. Patients will be extubated in the operating theatre and admitted to the PACU. Postoperative nausea and vomiting prophylaxis will be administered with dexamethasone 5 mg IV just before induction of general anesthesia. This will be supplemented, if necessary, by ondansetron 4 mg IV and further with alizapride 50 mg IV as rescue.

Postoperative pain in the PACU and on the ward will be treated with regular doses of acetaminophen 1 g IV around the clock (four times daily) and by a patient-controlled intravenous analgesia (PCIA) pump containing morphine at a concentration of 1 mg/mL and dehydrobenzperidol 0.05 mg/mL. The PCIA pump will be programmed as follows: no continuous infusion, a bolus dose of 1.5-mg morphine, a lockout interval of 8 min, and an hourly limit of 7.5 mg. If pain management on the PACU is inadequate, defined as an NRS pain score of more than 3 (0 [no pain] to 10 [worst imaginable pain]), additional boluses of 1-mg morphine IV will be administered by the PACU nurses with a total additional dose of morphine limited to 0.15 mg/kg. If pain management with morphine remains inadequate, an IV ketamine (Ketalar, Pfizer, New York, NY, USA) bolus (0.2 mg/kg) will be administered.

### Primary endpoint

The primary endpoint is the morphine consumption during the first 24 h postoperatively in milligrams and will be determined from the PCIA pump.

### Secondary endpoints

As secondary endpoint, the total morphine consumption in milligrams, during the first 72 postoperative hours, will be extracted out of the PCIA pump. Pain scores at rest will be assessed with the NRS score (0 = no pain, 10 = worst imaginable pain) and tested at regular time intervals: at the time of inclusion, in the PACU (T0 = arrival in PACU, T + 15 min, T + 30 min), and on the ward (twice daily: morning and evening until postoperative day 3). Pain scores during defined movement (first moving to a chair and sitting upright) will be registered. Time to first mobilization to a chair (in hours since T0) and time to first walk of 20 m (in hours since T0) will be noted in the patients’ study diary. The QoR-40 score will be calculated from the responses to a standard questionnaire at postoperative days 1 and 3. The QoR-40 is a widely used and extensively validated measure of quality of recovery. It is a 40-item questionnaire on quality of recovery from anesthesia that has been shown to measure health status after surgery [9, 10].

### Tertiary endpoints

Other endpoints include preoperative expected NRS pain score, postoperative nausea and vomiting score according to hospital protocol, number of administered postoperative anti-emetics, time to first meal, and time to first defecation. All block complications or adverse events will be registered.

### Summary of known and potential risks

The ESB is a plane block where a substantial dose of local anesthetic is used. As this technique has only recently been described, limited evidence regarding the potential risks of the block is available. The potential risks described below relate to the known risks of a plane block, facet infiltration, and intramuscular injection:Discomfort during punctureAllergy for the disinfectant or levobupivacaine (very rare 1:10,000–1:100,000)Infection at the skin, needle trajectory, or point of injection (very rare). The clinical presentation can be variable (e.g., redness at the puncture site or in extreme cases an intramuscular abscess). Therefore, the ESB will be performed under strict sterile conditions with a sterile gown, gloves and mask, and a sterile field.Bleeding: very rare with the use of an ultrasound-guided technique. When bleeding occurs, this will be noted by the surgeon.Neural damage: very rare since the target of the puncture is a muscular plane and not the nerve root or nerve ramus itselfLocal anesthetic systemic toxicity: since the doses are substantial, there is a clinically significant risk for local anesthetic systemic toxicity, as with any existing plane block. It can immediately be treated with intralipid. For this reason, the patient will be monitored during and after the placement of the ESB until the start of surgery. Intralipid should be available in any medical environment where regional anesthesia is performed.

